**Figure 1 figure1:**
[figure not shown]
Summary of the Peer Education and Peer Support (PEPS) program. PNTUM: Pham Ngoc Thach University of Medicine.

**Figure 2 figure2:**
[figure not shown]
Content of the peer-led education program. SMART: Specific, Measurable, Attainable, Realistic, and Timely.

### Control Group

The control group will receive the usual physical education curriculum of the school that comprises three 45-minute sessions (2 required and 1 voluntary) per week. One required session is theory-based and the other two are practical. All sessions are led by physical education teachers.

### Outcome Assessment

#### Primary Outcomes

The primary outcomes include acceptability and feasibility of the intervention to the target population. We will use 3 indicators to measure acceptability: (i) satisfaction, (ii) intent to continue use, and (iii) perceived appropriateness. Feasibility will be assessed by measuring 2 indicators: (i) barriers and facilitators experienced during the implementation of the intervention, and (ii) perceived barriers and facilitators to intervention implementation on a larger scale [23].

#### Secondary Outcomes

Secondary outcomes consist of changes in dietary behaviors, including skipping breakfast, consuming soft drinks and fast food, and fruit and vegetable intake among targeted students (ie, grade 6 students). Dietary intake will be measured by a validated self-administered youth Food Frequency Questionnaire developed and validated in Ho Chi Minh City [24]. This questionnaire, which can be completed in 20 minutes, records the usual frequency of consumption over the past 6 months of 160 foods representing 8 groups: (i) processed foods; (ii) rice, breads, and cereals; (iii) meat, fish, and other seafood; (iv) fruits and vegetables; (v) sweets and snacks; (vi) milk and dairy; (vii) drinks; and (viii) miscellaneous. Information about breakfast and the frequency of out-of-home meals will also be collected.

Secondary outcomes also include time spent in moderate-to-vigorous physical activity as well as time spent performing sedentary behaviors among targeted students (ie, grade 6 students). Level of physical activity is assessed by the Adolescent Physical Activity Recall Questionnaire, which has been validated in Vietnamese adolescents [25]. Activities are assigned a metabolic equivalent score according to the compendium of physical activities. The Adolescent Sedentary Activities Questionnaire, which has good-to-excellent reliability and good face validity in Vietnamese adolescents, is used to measure sedentary behaviors including time spent watching TV, playing games, on the computer, doing homework, and performing sedentary hobbies.

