#### Quantitative Data Collection

Dietary behaviors will be assessed using the validated Food Frequency Questionnaire developed for usage among junior high school students and used in previous studies. The secondary outcomes also include time spent on moderate-to-vigorous physical activity and time spent on sedentary behaviors among grade 6 students.

Time spent on moderate-to-vigorous activity will be assessed using the validated Physical Activity Questionnaire, and the time spent on sedentary behaviors will be assessed using the validated Sedentary Questionnaire that were used in previous studies among adolescents in Ho Chi Minh City [26,27].

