## Results

The first participant was enrolled in early September 2018. Recruitment was completed by March 2019. We delivered the peer education intervention at the start of each school year over 3 months for all new grade 6 adolescents in the allocated schools, followed by peer support and home engagement activities over 6 months until the end of the school year. However, the outcome assessments will be based on a cohort of adolescents only. There was a baseline assessment and 2 post-intervention assessments: the first immediately after the intervention to assess the short-term impact and the second at the end of the school year to assess the sustained impact on changes in adiposity, diet, and physical activity. In total, 326 grade 6 students were recruited. Data collection was completed in September 2019.

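### With a 6-month recall window, the diet questionnaire probably understates short-term change at the first follow-up if that follow-up falls at the end of the 3-month education phase

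*Protocol article*

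**What the plan says.** Under Secondary Outcomes, the Food Frequency Questionnaire "records the usual frequency of consumption over the past 6 months of 160 foods representing 8 groups". Quantitative Data Collection names the same instrument: "Dietary behaviors will be assessed using the validated Food Frequency Questionnaire developed for usage among junior high school students". Neither section mentions a version with a shorter reference period. Breakfast and out-of-home meals are collected as additional items, with no recall period given.

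The timeline is in the Results section and is repeated in the abstract: "We delivered the peer education intervention at the start of each school year over 3 months". The later phase is described in these words: "followed by peer support and home engagement activities over 6 months until the end of the school year". Two follow-ups come after baseline. The text on the earlier one reads: "the first immediately after the intervention to assess the short-term impact". The text on the later one, which also names diet as an outcome, reads: "the second at the end of the school year to assess the sustained impact on changes in adiposity, diet, and physical activity".

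Other sections give a different duration. Study Design and Discussion put education and support together at 6 months in total. Qualitative Data Collection places the end of the intervention 6 months after its start, but says so only for the acceptability and feasibility evaluation.

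**The concern.** A follow-up meant to capture short-term change needs a recall period that lies after exposure began. If the first follow-up is at month 3, a 6-month window reaches 3 months back before the programme. The answers then mix unexposed and exposed diet, and the between-arm difference shrinks toward zero.

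Two misreadings could follow. A small or null diet difference at the first follow-up could be taken as no short-term effect. A larger difference at the end of the year could be taken as growing benefit, when part of the rise comes only from the window moving into the exposed period. Both matter because the abstract and Discussion say the findings will inform a larger cluster trial.

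**Working it through.** **Inputs.** Recall window W = 6 months (Secondary Outcomes). Education phase 3 months, then support for 6 months to the end of the school year (Results). Grade 6 sessions in four consecutive weeks (Intervention Plan). Month 0 is the start of the education phase.

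**When is the first follow-up?** Support runs to the end of the school year, which is when the second assessment takes place. If the intervention in the Results timeline included support, the two follow-ups would coincide at month 3 + 6 = 9. Two distinct follow-ups arise only if the first comes at the end of education, about month 3.

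**Formula.** For follow-up at month t and exposure starting at month s, the exposed share of the window is [t − max(t − W, s)] / W. If students average evenly over the window and the change is complete at s, measured effect = true effect × exposed share.

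| Follow-up | Exposure starts | Window (months) | Exposed share |
|---|---|---|---|
| Month 3 | Month 0 | −3 to 3 | 3/6 = 50% |
| Month 3 | Last month of phase (assumed) | −3 to 3 | 1/6 = 17% |
| Month 3 | Last 4 weeks of phase (assumed) | −3 to 3 | (4 × 12/52)/6 = 0.92/6 = 15% |
| Month 9 | Month 0 or last 4 weeks of phase | 3 to 9 | 6/6 = 100% |
| Month 6 (alternative) | Month 0 | 0 to 6 | 6/6 = 100% |
| Month 6 (alternative) | Last 4 weeks of phase, i.e. month 2.08 | 0 to 6 | 3.92/6 = 65% |

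The 15% and 17% rows need an assumption. The article puts training of educators and peer leaders before the student sessions, but does not say where in the 3 months those four weeks fall.

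**Overlap with baseline.** If baseline is at month 0, its window is months −6 to 0. Months −3 to 0 then lie in both windows, which is half of each. The Sample Size section relies on a high correlation between baseline and follow-up. For diet at this round, part of that correlation could be shared recall time.

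**Artefact between follow-ups.** Let the true change D be complete at month 0 and constant afterwards. The first follow-up shows 0.5D and the second 1.0D, an apparent gain of 0.5D with no further change in behaviour.

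**Sensitivity to how students answer.** Let w be the weight that students give to the exposed part of the window, so that the measured effect is wD. With exposure from month 0, even averaging gives w = 0.5 and reporting only recent habits gives w = 1. The range is therefore 50% to 100%. With exposure in the last four weeks only, it is 15% to 100%. Nothing in the article narrows it.

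**The case against.** The strongest objection concerns timing. Three sections describe a 6-month intervention. If the first follow-up was at month 6, none of the window precedes the programme, and about 35% precedes the students' own sessions only if these came at the end of the 3 months. This stands as a condition. It does not displace month 3 as the natural reading of the Results timeline, because the one explicit statement of a 6-month end point concerns acceptability and feasibility only.

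Second, the 50% figure is not a strict ceiling. It depends on even averaging by 10- to 12-year-olds, and recency would raise it. This stands.

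Third, the consequence is limited. Diet is a secondary outcome in a pilot whose primary outcomes are acceptability and feasibility. Only questionnaire food items at one of two follow-ups are affected. The same window applies in both arms, so the mechanism dilutes an effect and does not create one. This also stands.

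A reader might infer more than the article supports:

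- **That the first follow-up cannot show any diet change.** An effect reduced to 50%, or even 15%, is smaller but not hidden by design.
- **That more than half of the window precedes the intervention.** On the Results timeline it is half. A larger share applies only to the time before the students' own sessions, and only if these started after month 0.
- **That physical activity and sedentary time are safe at this round.** The article gives no recall period for either questionnaire, so this can be neither asserted nor denied.
- **That the end-of-year window is clean for every student.** Recruitment ran from early September 2018 to March 2019 and individual start dates are not given. If a student's exposure began at month 6, the month-9 window would be only 3/6 = 50% exposed.

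**Conclusion.** The point holds with conditions. On the most natural reading of the Results timeline, half of the diet recall window at the first follow-up precedes the programme. The effect on soft drinks, fast food, fruit and vegetables is then probably understated: about 50% of the true change would show under even averaging, and about 15–17% if students were exposed only in the last month. Part of any gain from the first to the second follow-up may be a recall artefact.

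The size rests on three assumptions: a first follow-up at about month 3, even averaging over the window and, for the lower figures, late placement of the student sessions. Mainly recent reporting makes the attenuation smaller, and a month-6 follow-up removes most or all of it. The sections on duration must be reconciled before the size can be fixed. The primary aims of the pilot are not affected.

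**What to change.** 1. State when the first follow-up took place relative to the start of the education phase and of the grade 6 sessions. Reconcile Study Design, Qualitative Data Collection and Discussion with the Results timeline.
2. If it was about month 3, base questionnaire diet effects on the end-of-school-year assessment. Check from individual dates that the windows of late-recruited students also fall after their exposure began.
3. Still report the first-follow-up questionnaire results, as descriptive and with the attenuation stated. Do not use them as evidence for or against a short-term diet effect, and do not read the difference between rounds as growth. Give the recall window as the reason, because the decision comes after data collection ended in September 2019.
4. In the larger trial, schedule diet follow-up so that the whole recall window lies within the exposed period. Shortening the reference period is the alternative, but it departs from the instrument as validated, so it is a trade-off.

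For this pilot the cost is analysis and reporting wording, plus the loss of a formal short-term claim for questionnaire diet items. The recall period can no longer be changed for data already collected.

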### Sample Size

The sample size for the qualitative assessments (feasibility and acceptability) is based on the principle of reaching data saturation. We will stop data collection and analysis at the point when no significant new data is generated. The quantitative assessments consist of approximately 200 grade 6 students, because we expect small follow-up losses and a likely high correlation between baseline and follow-up outcome measures.

### Intervention Allocation

The assignment of participants to the intervention or control group is based on the location and population size of the school. There are 2 intervention schools and 2 control schools. We allocated the interventions at the school level, but the outcome assessments will be at the individual level.

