**Methods:**

The Peer Education and Peer Support (PEPS) project is a pilot cluster randomized controlled trial with 2 intervention and 2 control schools. The intervention consists of 4 weekly education sessions of why and how to choose healthy food and drinks and how to be more physically active. Additionally, the intervention includes a school-based and online support system to help maintain student engagement during the intervention. We will use in-depth interviews with students, peer leaders, teachers, and parents; focus group discussions with peer educators; and direct observation of the school environment and peer leaders’ interactions with the students. Acceptability and feasibility of the intervention will be assessed. We will also quantitatively assess limited efficacy by measuring changes in student’ physical activity levels and dietary behaviors.

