## Methods

### Study Design

This is a pilot cluster randomized controlled trial in which the intervention combines a peer education and peer support system for a total of 6 months.

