### Study Settings

We will select one intervention school in the city center area (District 5) and another intervention school in a suburban location (District 2). Similarly, one control school located in a city center area (District 11) and another control school located further away from the city center (Tan Binh District) will be selected.

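### The trial is labelled cluster randomized, but its only allocation statement assigns schools by location and size and names no random step; the label and the text must be reconciled

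*Protocol article*

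**What the plan says.** The Study Design section gives the label: "This is a pilot cluster randomized controlled trial". The title uses the same term, and the Methods part of the abstract says that the project "is a pilot cluster randomized controlled trial with 2 intervention and 2 control schools".

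The Intervention Allocation section is the only place that says how arms were assigned: "The assignment of participants to the intervention or control group is based on the location and population size of the school". It adds: "We allocated the interventions at the school level, but the outcome assessments will be at the individual level".

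Study Settings introduces each school with its arm and district already attached. For the intervention arm: "We will select one intervention school in the city center area (District 5) and another intervention school in a suburban location (District 2)". For the control arm: "one control school located in a city center area (District 11) and another control school located further away from the city center (Tan Binh District)".

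The Objective in the abstract lists efficacy on diet and physical activity as an additional aim. Statistical Methods plans linear and logistic regression to estimate the intervention's effect on the secondary outcomes, with sex, age and BMI as example covariates. Primary Outcomes names acceptability and feasibility, which Qualitative Data Collection assesses through interviews, focus groups and observation.

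**The concern.** A cluster randomized trial assigns clusters by chance. Location and size can serve as strata or matching factors within which chance operates, but the allocation section gives them as the basis of assignment itself and names no chance element. Either the label or the allocation text therefore needs correcting.

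What is at stake is how the secondary effect estimates may be read. Under randomization, differences between schools at baseline are due to chance, and the comparison has a causal interpretation by design, however imprecise it is with four schools. Under assignment by school characteristics that protection is absent, and a causal reading needs untestable assumptions about the schools and their districts. Readers, evidence synthesists and the planners of the larger trial that this pilot is meant to inform would take the label at face value.

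**Working it through.** The check is a comparison of text. No stated sample size, power or alpha figure is involved, so there is no planned figure to reproduce.

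**1. Label against rule**

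| Place in the article | What it implies about assignment |
|---|---|
| Title; abstract, Methods; Study Design | Clusters randomized |
| Intervention Allocation | Assigned by school location and population size |
| Study Settings | Intervention: Districts 5 and 2. Control: District 11 and Tan Binh |
| Rest of the article | No draw, sequence or within-stratum randomization described |

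The first row cannot stand with the second as they are worded.

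**2. What Study Settings does and does not show.** Each arm has one school described as central (District 5; District 11) and one further out (District 2; Tan Binh). Type of location is balanced between arms, so it does not determine the arm. The four schools are in four districts, so district is tied to arm. School size is not linked to an arm here; it appears only in Intervention Allocation.

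**3. Whether adjustment repairs it.** Sex, age and BMI describe the student. They can correct for a different mix of students but not for differences that act at school or district level. With one school per district and two schools per arm, there is very little information from which to separate such differences from the intervention. The covariate list is illustrative, so others may be planned, but the same limit applies.

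**4. What a random draw would have looked like** (context only)

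- Unrestricted, two of four schools: C(4,2) = 6 possible assignments; smallest two-sided randomization p-value 2/6 = 0.33.
- Within a central and an outer pair: 2 × 2 = 4 possible assignments; smallest two-sided p-value 2/4 = 0.50.

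The rule as written names one assignment and gives no set of possible assignments, so it supplies no randomization distribution.

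**5. Between-school variation** (context only). With two schools per arm and total outcome variance 1, the variance of the arm difference due to school effects is ICC × (1/2 + 1/2) = ICC, so its SD is √ICC. The article gives no ICC. Over an assumed range:

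- ICC 0.01: √0.01 = 0.10 outcome SDs
- ICC 0.02: √0.02 = 0.14
- ICC 0.05: √0.05 = 0.22
- ICC 0.10: √0.10 = 0.32

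These values apply to any comparison of two schools with two schools, including a properly randomized one. They show the cost of having four clusters and do not measure bias from non-random assignment. The outcomes are also defined as changes, and the article expects baseline and follow-up to be highly correlated, so stable school differences would be partly removed.

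**The case against.** The strongest defence is that the wording is loose and the design sound. One central and one outer school per arm is what matching or stratifying on location would produce. The article was published in June 2020, after data collection ended in September 2019, and it mixes tenses: schools are to be selected in one section and have been allocated in another. Study Settings could therefore report the result of a completed draw within pairs. The mechanics of a draw are also something that a condensed article may leave to the full protocol.

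Much of this stands. A reader might infer that the trial is established as non-randomized, that arms were fixed by district before schools were chosen, or that intervention schools were picked because they suited the programme. The document supports none of these. It does not settle the order of events, it does not exclude a draw within pairs, and it says nothing about suitability. The delayed-intervention offer to control schools concerns participation, not choice of arm.

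What the defence does not remove is the conflict. Silence about sequence generation would be excusable in an article. A positive statement that assignment rests on location and size is not silence, and it disagrees with the label.

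It is also fair to say that the consequence is limited. The primary outcomes do not depend on randomization, and the abstract itself calls the quantitative assessment one of limited efficacy.

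**Conclusion.** The point holds as a contradiction to be reconciled. The document labels the trial cluster randomized, states a non-random basis for assignment, attaches named districts to arms and describes no random step. Unless a draw is documented, randomization cannot be invoked for the secondary diet, physical activity and sedentary effect estimates. An adjusted non-randomized comparison with stated assumptions remains possible. The acceptability and feasibility findings are unaffected.

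The size of any bias from non-random assignment cannot be computed from the document, and neither can its direction. A reader might take 0.10 to 0.32 SD as that size. It is not: it rests on assumed ICCs and would arise equally if these four schools had been randomized.

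The conclusion rests on the text alone and needs none of those figures. It should be corrected before results are reported, because the design label governs how every effect estimate is read.

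**What to change.** First establish what was done, then make the sections agree.

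- **If schools were drawn at random:** state the draw in Intervention Allocation and Study Settings, with location and size described as matching or stratification factors and the districts by arm given as its result.
- **If they were not:** change the title, abstract and Study Design to a non-randomized (quasi-experimental) controlled pilot. Report the secondary effects as exploratory adjusted associations open to school-level confounding, and show results by school within the central pair and the outer pair.
- **In either case:** check that the registry entry, which was not available for this review, agrees with the corrected description.
- **For the follow-on trial:** pair schools by location and size and randomize within pairs.

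For the present study the cost is a revised paragraph or a revised label, plus a by-school display of data already collected. The downside of relabelling is a weaker design description.
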